### 2.6. Further Analysis

Depending on the result of each protocol a superiority trial analysis will be proposed to compare the effects of both approaches. The study will confirm the superiority of one of both protocols if the difference of the two means of King’s Pain Scale reduction is statistically significantly different at the 5% level (*p* < 0.05) two-sided and if the two-sided 95% confidence interval for the difference between the means excludes zero.

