The mental representation techniques included in the protocol will be Action Observation (AO) and Motor Imagery (MI). In the same way, the combination of AO and MI has shown to synergically increase cortical excitability [27], influencing the activation of cortical areas such as M1 and DLPFC [28]. Specifically in PD, they also have demonstrated to produce corticomotor facilitation [29]. In addition, mental representation training can produce neurophysiological activity similar to actual exercise training [30], which have shown to decrease the intensity and severity of pain in PD patients [31].

There are no studies correlating effects of pain non-invasive neuromodulation with complete neuropsychological evaluation including computerized reaction time tasks and extensive neurophysiological measures such as direct cortical excitability evaluation using TMS and connectivity based in EEG entropy analysis. All these features have been described to be altered in PD and Pain.

The main aim of this study is to conduct two independent parallel randomized controlled trials based on both neuromodulation techniques targeting changes in 1. validated general and specific PD related pain scales 2. psychophysical measurements of pain modulation mechanisms and 3. wide neuropsychological and neurophysiological evaluation. Our main hypothesis is that both active neuromodulation techniques will be superior to their respective control placebo interventions. If this hypothesis is confirmed a further analysis of superiority will be proposed among both protocols.

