## Figures and Tables

**Figure 1 brainsci-11-00065-f001:**
[figure not shown]
Schematic representation of both tDCS-based study and AO+MI-based study experimental procedures. It includes the days of the week and duration of each block of outcomes measurement in pre- and post-evaluation (KPDPS, King’s Parkinson’s Disease Pain Scale; BPI, Brief Pain Inventory; CPM, Conditioned Pain Modulation; TS, Temporal Summation; PPT, Pain Pressure Threshold; Psychological measures: Thursday/60–90 min; and Neuropsychological, Functional, Neurophysiological measures: Friday/120 min) and each treatment option (Experimental or Control group: Monday to Friday/10 sessions with the duration of each specific protocol, described in intervention protocols).

**Table 1 brainsci-11-00065-t001:** Additional inclusion and exclusion criteria for the transcranial direct current stimulation (tDCS)-based Study.

Inclusion Criteria	Exclusion Criteria
Older than 18. Neuroimaging study without previous pathologies. Score > 5 in transfers (bed to chair and back) item in Barthel Index. Score = or > 24 in Mini-Mental State Examination. Tolerability for the application of electrotherapy. Able to provide informed consent to participate in the study.	History of neurologic disease different from PD. Presence of non-related to PD pain. Dermatologic problems, wounds, or ulcers in the electrode’s application area. Presence of implants or metal pieces in the head. Presence of cardiac pacemaker, vagal, brain or transcutaneous stimulators, medication pumps, ventriculoperitoneal shunts or aneurysm clips. Significative difficulties in language. History of alcohol or drugs abuse. Non-controlled medical problems. Pregnancy. Epilepsy.

PD, Parkinson’s Disease.

**Table 2 brainsci-11-00065-t002:** Additional inclusion and exclusion criteria for AO+MI-based study.

Inclusion Criteria	Exclusion Criteria
Older than 18. Neuroimaging study without previous pathologies. Score > 5 in transfers (bed to chair and back) item in Barthel Index. Score = or > 24 in Mini-Mental State Examination. Able to provide informed consent to participate in the study.	History of neurologic disease different from PD. Presence of non-related to PD pain. Dermatologic problems, wounds, or ulcers in the electrode’s application area. Significative difficulties in language. History of alcohol or drugs abuse. Non-controlled medical problems. Pregnancy.

PD, Parkinson’s Disease.

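### Section 2.6 would confirm superiority of one therapy over the other from two separately randomised trials, without saying that each trial's control response is removed

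*Protocol article*

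**What the plan says.** The Introduction sets out to "conduct two independent parallel randomized controlled trials". Sections 2.1.1 and 2.1.2 give each its own randomisation, ethics code and registration: a-tDCS against s-tDCS in one, AO+MI-BCI against AO-control in the other.

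The Introduction then announces a comparison across the trials: "If this hypothesis is confirmed a further analysis of superiority will be proposed among both protocols". Section 2.6 repeats this, making it depend on how each trial turns out, and fixes a decision rule that begins: "The study will confirm the superiority of one of both protocols if the difference of the two means of King’s Pain Scale reduction". The threshold for that difference is p < 0.05 on a two-sided test. A second condition asks that the matching 95% interval leave out zero.

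Section 2.6 does not say which arms supply the two means, mentions neither control group and names no covariates. Section 2.1 promises that disease severity and daily dopaminergic dose will be controlled in the final analysis, but Section 2.6 does not refer to this.

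**The concern.** Randomisation protects each active-against-control contrast. It does not protect a contrast between the two active arms, because nobody is allocated between them. Three features make the gap matter for a self-reported pain score:

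- **Controls.** Section 2.2.1 uses sham current with the same electrode placement. Section 2.2.2 uses a video, omits the initial BCI step and instructs patients to observe and relax.
- **Active procedures.** One is passive stimulation. The other involves EEG set-up, classifier training and a virtual-reality game. Non-specific response could plausibly differ.
- **Eligibility.** Some Table 1 criteria are absent from Table 2, for example "Presence of implants or metal pieces in the head", epilepsy, implanted stimulators and tolerability of electrotherapy.

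The Introduction says that the placebo groups are there to remove expectation-related error. A rule that compares two raw reductions gives up that protection exactly where the protocol proposes to confirm a winner. At stake is a published head-to-head claim without randomised evidence behind it.

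**Working it through.** **The plan's own figures.** Section 2.6 gives no sample size, power or SD for this comparison, so there is no stated figure to reproduce. Section 2.4 gives 28 patients per trial before loss and 32 after, which is 14 or 16 per arm. The check uses 14 completers per arm, with 16 as a variant. The documents give no KPDPS SD and no expected placebo response, so the shifts below are assumptions in units of the SD of change.

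**Step 1: the two criteria are one test.** A two-sided p < 0.05 and a 95% CI that excludes zero are the same condition for a difference in means. The second adds no safeguard.

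**Step 2: plain reading (raw active-arm reductions).** Let the two therapies have the same specific effect and let non-specific response or case mix differ by d SD between trials.

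- SE of the contrast = √(2/14) = 0.378 SD.
- Noncentrality = d / 0.378; 26 degrees of freedom; critical value 2.056.
- Probability of declaring superiority, from the noncentral t distribution:

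| Shift d (SD) | Noncentrality, 14 per arm | False superiority, 14 per arm | False superiority, 16 per arm |
|---|---|---|---|
| 0 | 0 | 5.0% | 5.0% |
| 0.25 | 0.66 | 9.8% | 10.5% |
| 0.5 | 1.32 | 24.7% | 27.8% |
| 0.75 | 1.98 | 48.0% | 53.7% |

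More patients make it worse, because the shift is bias rather than noise.

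**Step 3: the comparison is run only if both trials succeed.** Simulation with 14 per arm and 200,000 runs per setting; the comparison is made only when both active arms beat their own control on a two-sample t test of change. The specific effect is set at 0.8 or 1.27 SD (the latter gives about 90% power per trial).

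| Shift d (SD) | False superiority when the comparison is run | Overall, counting runs where it is not made |
|---|---|---|
| 0 | 2.7% to 3.9% | 0.7% to 3.1% |
| 0.25 | 7% to 9% | 2% to 7% |
| 0.5 | 23% to 24% | 6% to 19% |
| 0.75 | 49% to 51% | 14% to 39% |

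The lower overall figures belong to the 0.8 SD effect, where the comparison is seldom reached. Once it is run, the rates are close to Step 2.

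**Step 4: control-adjusted contrast.** (a-tDCS minus s-tDCS) minus (AO+MI-BCI minus AO-control).

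- SE = √(4/14) = 0.535 SD, which is 0.535/0.378 = 1.41 times the raw contrast.
- In 100,000 simulated runs, false superiority stayed at 5.0% to 5.1% for shifts of 0, 0.5 and 0.8 SD, given that the shift is additive and affects active and control arms alike.
- Difference detectable with 80% power, 52 degrees of freedom: (2.007 + 0.849) × 0.535 = 1.53 SD. Power at a true difference of 0.5 SD is about 15%.

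**The case against.** **Section 2.6 does not say which means it compares.** Its opening sentence speaks of the effects of both approaches, and Section 2.5 estimates each effect as active against control over time. A reader might infer that the plan definitely ignores the control arms. The text does not establish that; raw active-arm reductions are only the plainer literal reading. This objection stands, and under the other reading the Step 2 rates do not apply. It does not rescue the wording, because a control-adjusted contrast between separate trials with different controls is still indirect.

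**The populations may be close.** Both trials recruit from the same clinic with the same diagnostic, pain and age-stratification rules, ten ON-state sessions and the same outcome schedule. The extra Table 1 items look stimulation-related, and nothing in the documents ties them to KPDPS change. Although the trials are labelled triple- and double-blind, Section 2.1.2 also describes measures for patient, evaluator and statistician. Section 2.1 promises control of severity and dopaminergic dose. This weakens the case-mix argument. It does not touch a difference in non-specific response.

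**Conditional running.** A reader might infer that comparing the therapies only after favourable results inflates the error rate. Step 3 does not support this: with no shift, the rate among comparisons run is about 3% to 4%, below 5%.

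**It is a contingent further analysis.** True, and it lowers the severity. But only the trigger is tentative; the rule itself says that superiority will be confirmed.

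**Conclusion.** The rule is wrong as written: two independently randomised trials cannot confirm that one therapy is superior to the other. On the plain reading, false superiority is about 10%, 25% or 48% for shifts of 0.25, 0.5 or 0.75 SD whenever the comparison is run. Those rates assume 14 completers per arm, equal specific effects, a common SD and additive shifts whose size the documents do not give. On the control-adjusted reading the additive bias disappears, but the comparison remains indirect, and at this size only a difference of about 1.5 SD would be detected with 80% power.

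Severity is moderate. A reader might infer that the trials' main results are compromised; they are not, since the main hypothesis, sample sizes and primary ANOVA all concern each active arm against its own control.

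**What to change.** In Section 2.6:

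1. Delete the statement that superiority will be confirmed, together with the p < 0.05 decision rule. Call the comparison exploratory and non-randomised.
2. Define the contrast as (a-tDCS minus s-tDCS) minus (AO+MI-BCI minus AO-control) in KPDPS change. Estimate it as the trial-by-arm interaction in a pooled model adjusted for baseline KPDPS, age group, and the disease severity and dopaminergic dose already promised in Section 2.1.
3. Report the estimate with its 95% CI.
4. State that it is unbiased only if the two different controls capture non-specific response equally.

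The cost is a short rewording and one extra model. The CI will be about 1.4 times wider than for the raw contrast. A confirmatory answer would need a trial that randomises patients between the two therapies.

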### 2.7. Dissemination Plans

All results will be published in specialized scientific journals. The final dataset from these studies will be anonymized and accessible after publication upon justified request to the main researchers. Results will be made public to the general public through the social media of our institution.

## 3. Discussion

Our studies are very relevant in the quest for an effective non-pharmacological management of pain in PD. This symptom has a high prevalence and impacts negatively in the quality of life of affected subjects. Moreover, nowadays this matter becomes even more relevant because lack of physical activity produced because of pandemic mobility restrictions could increase pain. 49.7% of Spanish PD patients report having suffered from pain every day during the COVID-19 pandemic [67].

We propose two treatment strategies whose action mechanisms are compatible with the hypothesized pain mechanisms implied in PD and have been effective in the management of pain in other chronic pain conditions. Furthermore, both approaches are proposed to be applied in combination with conventional treatments, mainly based on exercise and dopaminergic medication, in order to enhance their effectiveness through predisposing the cortex to be more easily excited. Finally, both treatments, after the configuration and explanation, can be applied at home, facilitating independence and self-management, and maximizing the time out of medical centers. Future studies may combine tDCS over M1 with AO+MI-BCI if the results of both studies are satisfactory.

Additionally, our protocols will potentially give us valuable information about pain mechanisms and enlighten new solutions for its management in PD patients. For this purpose, firstly, we propose an integral evaluation of pain, not only measuring clinical pain, but also assessing the functioning of the descending pain modulatory system, the nociceptive pathways excitability, and possible peripherical and central hyperalgesia, establishing correlations between them. Secondly, we also have the intention to figure out whether emotional, cognitive, functional, neuropsychological, or neurophysiological aspects can influence on pain and its central processing in PD patients.

## Figures and Tables

**Figure 1 brainsci-11-00065-f001:**
[figure not shown]
Schematic representation of both tDCS-based study and AO+MI-based study experimental procedures. It includes the days of the week and duration of each block of outcomes measurement in pre- and post-evaluation (KPDPS, King’s Parkinson’s Disease Pain Scale; BPI, Brief Pain Inventory; CPM, Conditioned Pain Modulation; TS, Temporal Summation; PPT, Pain Pressure Threshold; Psychological measures: Thursday/60–90 min; and Neuropsychological, Functional, Neurophysiological measures: Friday/120 min) and each treatment option (Experimental or Control group: Monday to Friday/10 sessions with the duration of each specific protocol, described in intervention protocols).

**Table 1 brainsci-11-00065-t001:** Additional inclusion and exclusion criteria for the transcranial direct current stimulation (tDCS)-based Study.

Inclusion Criteria	Exclusion Criteria
Older than 18. Neuroimaging study without previous pathologies. Score > 5 in transfers (bed to chair and back) item in Barthel Index. Score = or > 24 in Mini-Mental State Examination. Tolerability for the application of electrotherapy. Able to provide informed consent to participate in the study.	History of neurologic disease different from PD. Presence of non-related to PD pain. Dermatologic problems, wounds, or ulcers in the electrode’s application area. Presence of implants or metal pieces in the head. Presence of cardiac pacemaker, vagal, brain or transcutaneous stimulators, medication pumps, ventriculoperitoneal shunts or aneurysm clips. Significative difficulties in language. History of alcohol or drugs abuse. Non-controlled medical problems. Pregnancy. Epilepsy.

PD, Parkinson’s Disease.

**Table 2 brainsci-11-00065-t002:** Additional inclusion and exclusion criteria for AO+MI-based study.

Inclusion Criteria	Exclusion Criteria
Older than 18. Neuroimaging study without previous pathologies. Score > 5 in transfers (bed to chair and back) item in Barthel Index. Score = or > 24 in Mini-Mental State Examination. Able to provide informed consent to participate in the study.	History of neurologic disease different from PD. Presence of non-related to PD pain. Dermatologic problems, wounds, or ulcers in the electrode’s application area. Significative difficulties in language. History of alcohol or drugs abuse. Non-controlled medical problems. Pregnancy.

PD, Parkinson’s Disease.

## Data Availability

The data presented in this study will be available on request from the corresponding author.
